#### Grip strength

Grip strength will be measured using a digital grip strength dynamometer (T.K.K. 5401 GRIP-D; Takei, Japan). The measurement will be performed in the sitting position, with the shoulder joint placed at 0° and the elbow joint placed in extension, twice on each side. The maximum value of the results obtained will be used in the analysis. Grip strength is correlated with the overall muscle strength [91]. The reliability of the measuring instruments has been reported [92, 93].

#### Plan to promote participant retention and completion of the follow-up

The study planners will inform the participants about the details of the study schedule and the importance of the study to prevent participant dropout and facilitate follow-up [94]. Furthermore, all interventions and outcome assessments will be performed free of charge. In addition, outcome assessments and information collection will be minimized, to reduce the burden on the hospitalized patients. Participants who meet the criteria for refusal to continue the study or for discontinuation of the intervention will be invited to participate in a postintervention evaluation. These suggestions will be highlighted and explained to the participants during informed consent.

### Data management, confidentiality, and access

To ensure data accuracy, the participants’ data will first be transcribed onto paper. Two independent researchers will then enter the data into an Excel spreadsheet. These data entries will be performed on a computer that is not connected to the Internet. All information entered will be stored on a password-protected USB stick. The next step will be the checking of the collected data by researchers other than the two researchers who entered the data for accuracy, missing data, and data consistency [94]. The paper data created previously will be stored in a lockable storage facility at Gunma University, and the electronic data will be stored in a separate lockable cabinet. Backups of electronic data will be created on hard drives that are not connected to the Internet. The participants’ data will be anonymized and managed using random codes. These data will be stored for 10 years after the publication of the article and will be properly erased after the storage period. Only the principal investigator and data manager will have access to the collected data. The principal investigator and data manager will investigate data issues and prepare the dataset for statistical analysis. After publication, only the principal investigator and selected groups of individuals will have access to the dataset. No computer at Gunma University that is connected to the Internet will be used for statistical analysis.

### Statistical methods

The ITT principles will be followed during the analysis of all assigned participant data. The primary and secondary outcomes will be compared between the two groups using linear mixed models with a restricted maximum-likelihood estimation method for repeated measurement analysis. Group, time, and their interaction will be used as fixed-effect variables, whereas the participants will be used as random-effect variables. All significance levels will be set at *P* < 0.05 using two-tailed tests. No subgroup analysis is planned at this time. All analyses will be performed using the latest version of SPSS. The effect size (Hedge’s g) between groups will also be calculated [95, 96].

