#### Inclusion criteria

Men and women.Patients admitted to the acute wards of the Fujioka General Hospital.Individuals aged 65 years or older.Patients with cardiac disease (coronary artery disease, heart failure, heart valve disease, and arrhythmia).Patients with a total score of 10 or more on the Japanese version of the Beck Depression Inventory-II [70].Persons with sufficient cognitive ability to understand the content and purpose of the research.Persons who provided written consent before participation in this study.Patients with New York Heart Association functional classification (NYHA classification) degrees I–III.

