### Outcomes

The primary outcome will be the change in the scores on the Japanese version of the BDI-II at 1 week after the baseline assessment [75]. In turn, the secondary outcomes will be the changes in the minimum amount of exercise at which heart failure symptoms appear on the Specific Activity Scale (SAS) [76], New York Heart Association functional classification (NYHA classification) [77], as well as grip strength at 1 week after the baseline assessment.

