### Recruitment timeline

The study will be conducted at the Fujioka General Hospital in Gunma, Japan, from October 2023 to March 2027. The researcher will distribute a brochure with a brief description of the study to potential participants, to encourage their participation. Potential participants will be assessed for eligibility through interviews and questionnaires, and enrolled in the study after baseline assessments (BDI-II and SAS, NYHA classification, and grip strength assessment). The baseline and eligibility assessments will be performed by the researcher within 1 week of admission to the acute wards. The participants will be randomly assigned to the Experimental or Control group after the eligibility and baseline assessments. Both groups will then receive a 10-min video-viewing intervention once per day, five times per week for 1 week. The participants will undergo remeasurements for second BDI-II and SAS, NYHA classification, and grip strength at 1 week after the intervention. A flowchart of the study design is shown in Fig. 3 [78]. The assessment schedule is provided in Table 1 [79].

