### Sample size

There are no data on SPSRS interventions for patients with cardiac disease and StD admitted to acute wards, which hampers the estimation of the sample size based on actual data. Although a formal sample size calculation is not required in a pilot study [68], a sample size of 15–20 persons should be maintained in a pilot study for conducting a subsequent full-scale study [80]. Therefore, the goal of this study was to recruit 15 participants per group, for a total of 30 participants.

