### Allocation

The participants will be randomly assigned to the Experimental or Control group in a 1:1 ratio after the eligibility criteria check and baseline assessment. Using a computer (Excel software), a randomized list will be generated using the permuted block method. To ensure allocation concealment, the block sizes will not be disclosed until after trial completion. The generation of the randomized list will be performed by a third party not involved in the study. Throughout this process, the participants, evaluators, and intervention implementers will be denied access to information that might reveal the assignments. The randomized list will be provided to the Central Registration Center located at Gunma University, for random assignment.

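### The planned mixed model gives each arm its own baseline mean, so its primary contrast is a change-score comparison: valid, but usually less precise than a baseline-adjusted one and moved by chance baseline imbalance

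*Protocol article*

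**What the plan says.** All references are to the protocol article.

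- **Outcomes:** "The primary outcome will be the change in the scores on the Japanese version of the BDI-II at 1 week after the baseline assessment". Table 1 lists BDI-II at baseline and at 7 days only.
- **Statistical methods:** outcomes are "compared between the two groups using linear mixed models with a restricted maximum-likelihood estimation method for repeated measurement analysis", and "Group, time, and their interaction will be used as fixed-effect variables, whereas the participants will be used as random-effect variables". Tests are at the 0.05 level, "using two-tailed tests". The section does not say which term is the primary test. Because the outcome is defined as change, the interaction is the term that fits it.
- **Recruitment timeline:** "The participants will be randomly assigned to the Experimental or Control group after the eligibility and baseline assessments". The Allocation section agrees. It describes permuted blocks and states no stratification.
- **Inclusion criteria:** "Patients with a total score of 10 or more on the Japanese version of the Beck Depression Inventory-II".
- **Sample size:** "the goal of this study was to recruit 15 participants per group, for a total of 30 participants".

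Nowhere is baseline BDI-II entered as a covariate, and nowhere are the two baseline means held equal.

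**The concern.** Baseline BDI-II is recorded before allocation, so the two arms have the same expected baseline score by design. The listed fixed effects make no use of this. The group term lets the arms differ at baseline, and the interaction then subtracts the whole of any observed baseline difference, as if every point at baseline persisted as a full point at 1 week. When the true slope of the 1-week score on baseline is below 1, this over-corrects.

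Two things are at stake. The first is precision, which is scarce with 15 per arm. The second is the single estimate this pilot will produce: it is meant to indicate preliminary efficacy and help plan a full-scale trial, and part of it could be baseline luck that data already collected would remove.

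**Working it through.** **Inputs from the protocol:** two time points, 15 per arm, two-sided 0.05, BDI-II of 10 or more at entry. **Assumed, because the protocol gives none:** SD 7 points, true difference 5 points, baseline-to-follow-up correlation rho from 0.4 to 0.9, equal variances. The protocol states no power or effect size, so there is no figure of its own to reproduce.

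**1. What the interaction estimates.** A REML model with group, time, their interaction and a random intercept was fitted to simulated complete data with 15 per arm, alongside a two-sample comparison of change scores.

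| rho | Interaction (SE) | Change-score difference (SE) |
|---|---|---|
| 0.3 | -0.59412 (0.37335) | -0.59412 (0.37335) |
| 0.6 | -0.22451 (0.26526) | -0.22451 (0.26526) |
| 0.8 | -0.04787 (0.18724) | -0.04787 (0.18724) |

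The two are identical. With missing 1-week scores the identity is no longer exact, but each arm still keeps its own baseline mean.

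**2. Precision without range restriction.** Per participant, in units of SD², the variance of change is 2(1 - rho) and the ANCOVA residual variance is 1 - rho². Their ratio is 2/(1 + rho). ANCOVA also pays for estimating the slope, by a factor 1 + 1/(2n - 4) = 1 + 1/26 = 1.038. At rho 0.5 the net ratio is 1.333/1.038 = 1.28.

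**3. Precision with the entry cut-off.** Where 10 points falls in the distribution is unknown. If it falls at the mean of a normal baseline, the baseline variance shrinks to 1 - 2/π = 0.363 of its value (SD factor 0.603), while the slope stays at rho. The ratio becomes 1 + 0.363(1 - rho)/(1 + rho), again divided by 1.038. At rho 0.5 this is 1.121/1.038 = 1.08. At 0.9 it is 1.019/1.038 = 0.98.

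Simulated values (20,000 replicates) agree with these formulas to within about 0.02:

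| rho | Ratio, unrestricted | Power, change vs ANCOVA | Ratio, truncated at mean | Power, change vs ANCOVA |
|---|---|---|---|---|
| 0.4 | 1.36 | 41% vs 53% | 1.12 | 49% vs 53% |
| 0.5 | 1.28 | 48% vs 58% | 1.07 | 54% vs 58% |
| 0.6 | 1.20 | 56% vs 63% | 1.05 | 62% vs 64% |
| 0.8 | 1.07 (formula) | – | about 1.00 | 87% vs 87% |
| 0.9 | 1.01 (formula) | – | 0.98 | – |

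**4. Effect of a chance imbalance.** The SE of the baseline difference is sqrt(2/15) = 0.365 SD. The chance of a difference above 0.5 SD in either direction is 0.17. Given an imbalance D, the change-score estimate moves by -(1 - slope) x D. For a one-SE imbalance at slope 0.5:

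- unrestricted: 0.365 x 7 = 2.56 points, so a shift of 0.5 x 2.56 = 1.3 points;
- truncated: SD 0.603 x 7 = 4.22, then 0.365 x 4.22 = 1.54 points, so a shift of 0.8 points.

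**5. Validity.** Simulated under no effect, the planned test rejected in 4.8% to 5.3% of runs and ANCOVA in 5.0% to 5.4%.

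**The case against.** The defence is substantial, and most of it stands.

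- **The model is standard and valid.** A reader might infer from the imbalance argument that the planned test is biased or has inflated type I error. The calculation does not support that: over all randomisations the estimate is unbiased and the error rate is nominal. The shift is conditional on the imbalance that happens to occur.
- **The entry cut-off does not make matters worse.** It is tempting to say that selecting on BDI-II brings in regression to the mean and so biases the comparison. Regression to the mean acts equally on both randomised arms, and truncation narrows the baseline spread, which reduces the advantage of adjustment. The unrestricted power gaps of 7 to 12 points are therefore an upper case.
- **The correlation may be high.** The Discussion notes that BDI-II covers the past 2 weeks, and follow-up is at 1 week, so the two recall windows overlap. That points towards higher correlation, where the gain is small. The protocol gives no value, so this is plausibility only.
- **Adjustment is not always more precise.** With truncation and rho 0.9, ANCOVA is slightly worse (ratio 0.98).
- **The group main effect.** One might worry that this term, which averages in the pre-treatment score, would be read as the treatment effect. Nothing in the protocol says so, and defining the outcome as change points to the interaction.
- **It is a pilot.** There is no power calculation, and limited power is conceded. This lowers the stakes without removing the point, since the plan still specifies significance tests and a between-group effect size.

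What remains is that the listed fixed effects leave the pre-randomisation baseline unadjusted. An analysis plan that is not shown could add it, but it would then be changing the model that the protocol states.

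**Conclusion.** The point holds as one of efficiency and of sensitivity to baseline luck. It is not a fault of validity. How much there is to gain rests on an unknown correlation and on where the cut-off of 10 falls in the baseline distribution: clearly worthwhile at moderate correlation with little range restriction, modest if the cut-off truncates near the mean, and nil or marginally negative at correlations of 0.8 to 0.9 under that truncation. The conditional shift is the more persistent part, because truncation narrows the imbalance but does not bring the slope up to 1. At an assumed slope of 0.5, a quite ordinary imbalance moves the result by roughly a sixth (0.8/5) to a quarter (1.3/5) of the assumed 5-point effect. The change is worth making before analysis because it uses only data already collected.

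**What to change.** In Statistical methods, keep the REML mixed model but hold the baseline mean common to both arms: time and group-by-time as fixed effects, no group main effect, and an unstructured 2x2 covariance for the two scores, which takes the place of the random participant effect. One caution on coding: with categorical factors, deleting the group term while keeping the full interaction merely re-expresses the same four means. The treatment term should be an indicator that is 1 only for the Experimental group at 1 week. Name the adjusted 1-week BDI-II difference, with its 95% CI, as the primary contrast. Do the same for grip strength.

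This model keeps participants whose 1-week score is missing, in line with the stated intention to analyse everyone assigned. ANCOVA of the 1-week score on group and baseline BDI-II is an alternative that nearly coincides when follow-up is complete. It is not equivalent when scores are missing, because it drops participants who have only a baseline score.

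The cost is about one degree of freedom and a protocol amendment, which the Ethics and dissemination section requires both ethics bodies to approve. No new data or software are needed.

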### Data monitoring and auditing

At the present time, no formal data oversight committee has been established and no data audit is planned. Furthermore, no interim analysis of the impact of the intervention is planned.

### Ethics and dissemination (approval, protocol amendments, and consent)

This study was approved by the Ethical Review Board for Medical Research Involving Human Subjects of Gunma University (approval number: HS2023-050). The study was also approved by the Ethical Review Committee of Fujioka General Hospital (approval number: 338). Before participation in the study, the subjects will be briefed by the principal investigator or a research collaborator on the study via written research briefing materials. Any changes to the research plan must be approved by the Ethical Review Board for Medical Research Involving Human Subjects of Gunma University and the Ethical Review Committee of Fujioka General Hospital. Before enrolling the participants in the study, the researcher will explain the benefits and risks of participation, ensure that the participants are aware of the benefits and risks of the intervention, and obtain consent to participate. Participants who agree to participate in the study must provide written informed consent.

### Ancillary and posttrial care

The participants may contact the researcher at any time during the study period. After the 1-week intervention, the researchers will continue to track the progress of the participants and document the changes in their physical and mental health. There is no guarantee that unforeseen problems will not arise during or after the study. In the event of serious complications or health problems, the necessary treatment will be provided within standard insurance coverage. The cost of treatment will be borne by the participant, as is the case with regular treatment.

### Dissemination policy

The results of this research, regardless of their validity, will be submitted to peer-reviewed journals. In addition, the research results and their scientific significance will be reported and disseminated at academic conferences.

## Discussion

This study is a pilot RCT aimed at investigating the effect of the SPSRS intervention on depressive symptoms in older patients with cardiac disease and StD who are admitted to acute wards. StD is a risk factor for increased mortality, incidence, rehospitalization rates, and severity of illness among older patients with cardiac disease. However, it has been suggested that the existing treatments, such as pharmacotherapy, for older patients with cardiac disease and StD do not adequately reduce depressive symptoms [32, 97–99]. Therefore, there is a need to identify alternative approaches for treating depressive symptoms in older patients with cardiac disease. The SPSRS website may be a new intervention strategy that can improve depressive symptoms in older patients with cardiac disease and StD. The SPSRS is a video-viewing website in which positive language stimuli are presented, and can be accessed through any Internet-enabled device. Therefore, the SPSRS intervention is less burdensome for the patients and interveners; has a low cost; is simple, novel, and guaranteed to be of similar quality for all participants; and can provide treatment to various individuals. Therefore, we designed a pilot RCT to investigate the preliminary efficacy of the SPSRS intervention among older patients with cardiac disease and StD. This pilot RCT was designed to enhance the scientific validity of full-scale RCTs. The results of this study will provide additional insights into the preliminary effectiveness and feasibility of the SPSRS intervention, and will allow us to identify the modifications and improvements that are necessary for a successful larger RCT.

This study has several strengths. First, this is the first pilot RCT to investigate the preliminary efficacy of the SPSRS intervention for improving depressive symptoms in older patients with cardiac disease and StD who are admitted to acute wards. This pilot RCT may lead to the development of a state-of-the-art treatment approach to improve depressive symptoms in older patients with cardiac disease presenting with StD, and can expand our knowledge of the benefits and limitations of intervention strategies for the management of depressive symptoms in this specific population. Second, the study has a high external validity, because it includes patients suffering from a variety of cardiac diseases.

This study also had several limitations. First, this study will be conducted on an open-label basis because of its nature. This may lead to a bias among the treatment providers, study participants, and evaluators. When interpreting the study results, it will be necessary to consider the effects of other factors, such as participant expectations and the relationship between the treatment provider and the patient, on depressive symptoms. Second, because this is the first study to examine the effect of the SPSRS intervention on older patients with cardiac disease and StD who are admitted to acute wards, no formal sample size calculations will be performed. This limitation may reduce the statistical power of the primary and secondary outcomes. Third, because this pilot RCT will be conducted at a single site exclusively, the sample is less representative, and not all findings obtained will apply to older patients with cardiac disease and StD who are admitted to acute wards [100]. Fourth, this study may underestimate the effects of SPSRS intervention on depressive symptoms in older patients with cardiac disease and StD. The intervention duration in this study was 1 week because the number of days of hospitalization should be considered in the acute care of patients with cardiac disease in Japan and the feasibility of data collection and the duration of possible rehabilitation intervention. The BDI-II is a self-report measure of depressive symptoms that assesses symptoms over the past 2 weeks; however, previous studies indicate that a 1-week intervention period can produce significant differences in the BDI-II [87–89, 101, 102]. For these reasons, we employed BDI-II in this study. However, considering that the BDI-II is a self-report measure of depressive symptoms that assesses symptoms over the past 2 weeks, we cannot dismiss the possibility that the intervention period of this study (one week) will result in little changes in depressive symptoms as measured by BDI-II. Finally, because the specific video to be viewed during the SPSRS is determined based on participant self-selection from a full range of videos, the differences in the participants’ video choices may have an impact on depressive symptoms.

## Conclusions

This pilot RCT is the first study to investigate the impact of an SPSRS intervention on depressive symptoms in older patients with cardiac disease and StD. This pilot RCT, which was designed according to an appropriately standardized procedure, will allow the evaluation of the potential of a larger trial to detect the effects of the SPSRS intervention on depressive symptoms in older patients with cardiac disease and StD. If the results of the intervention are positive, the SPSRS intervention may also become a new strategy to improve depressive symptoms in older patients with cardiac disease and StD.

## Data Availability

Not applicable.
